### Investigational products

All study cigarettes will be provided by the sponsor free of charge (Table 3). To achieve blinding, unbranded cigarettes and packs will be manufactured specifically for the study. All packaging will include the mandatory health warnings, details of yields and tax stamps. The control cigarettes will match the specifications of the commercial cigarettes supplied before switching, except for a visual but cosmetic difference (i.e., plain white tipping on the control versus cork patterned tipping on the commercial cigarette; Table 3). This will allow RTP and control smoker cohorts to see a noticeable change to their cigarettes without being able to determine which product they are receiving. The different cigarette products will be identifiable to the clinic pharmacy staff and investigators by study identification codes (Table 3) that will be printed on the packaging and on the individual cigarettes. The cigarette products will be stored in a locked, limited-access area under controlled temperature and humidity conditions.

**Table 3 T3:** Investigational products

**Study period**	**Control group**	**Test group**
Days 1–14	Lucky Strike Silver (ID W861) with mono CA filter, cork-print tipping and commercial tobacco blend	Lucky Strike Silver (ID W861) with mono CA filter, cork-print tipping and commercial tobacco blend
	*Yields using ISO methodology: 7 mg tar, 0.6 mg nicotine, 8 mg CO*	*Yields using ISO methodology: 7 mg tar, 0.6 mg nicotine, 8 mg CO*
Days 15–183	Lucky Strike Silver (ID H285) with mono CA filter, white tipping and commercial tobacco blend	RTP (ID G429) with triple CA/CR20/charcoal filter^a^, white tipping and study tobacco blend (20% non-tobacco sheet, 50% treated tobacco and 30% commercial blend).
	*Yields using ISO methodology: 7 mg tar, 0.6 mg nicotine, 8 mg CO*	*Yields using ISO methodology: 7 mg tar, 0.7 mg nicotine, 8 mg CO*^*a*^

*ID,* study identification code, *CA,* cellulose acetate, *CR20,* amine-functionalised resin filter additive, *CO,* carbon monoxide, *RTP,* reduced-toxicant prototype cigarette, *ISO,* International Organisation for Standardisation. ^a^to be confirmed.

### Study procedures at each visit

#### Screening

Participants who have signed informed consent forms will be eligible for screening. Medical history, smoking history and demographic data (e.g., sex, age, ethnic origin, etc.) will be recorded. Each participant will be required to provide proof of age with a form of identification accepted by MOMENTUM Pharma Services (i.e., national identity card or work or residence permit).

Participants will undergo the following assessments: physical examination, including measurement of height, weight, blood pressure, pulse rate and temperature; 12-lead electrocardiography; pulmonary function testing; clinical laboratory tests; testing for infection with hepatitis virus B and C and HIV; urine pregnancy test for women; urine drug screening; and alcohol breath test. Urine will be taken for cotinine testing to confirm whether participants are smokers or non-smokers. Other general observations and questioning may be added by the investigators.

#### Ambulatory visits

Participants in the smoking groups will visit the clinic on the first day of the first ambulatory period (Figure 1). Smoking subjects will be asked to confirm the ISO tar yield of their usual brand and smoking status of all subjects will be verified by a urine cotinine test. Participants will be given a diet sheet to which they will be asked to adhere during specified times in ambulatory periods (i.e. 48 h before each in-clinic evaluation). Participants will be supplied with cigarettes according to their assigned product (Table 3) and daily consumption rate, plus two packs, and asked to smoke only the supplied brand until their next visit. Smokers will be allowed to smoke *ad libitum*, rather than according to a pre-specified quantity or timetable.

Each participant will be trained how to use an electronic diary in which he or she will be asked to document cigarette consumption, diet, exercise, medications and any other health-related issues on every ambulatory day. Participants will be required to bring the diary to every clinic visit.

Further ambulatory clinic visits will be made on days 31, 62, 95, 124, 144 and 165 (Figure 1). During these visits, diary entries will be checked, any protocol violations (e.g. consumption of cigarettes that were not supplied by the sponsor, significant health-related events or intake of excluded medications) will be assessed and decisions made about further participation in the study. Urine samples will be taken and tested for cotinine. Cigarette butts will be collected for analysis and the numbers of butts will be compared with diary entries and recorded. Participants will be supplied with further study cigarettes (normal daily consumption x number of days, plus two packs) and reminded to smoke only those until their next visit. They will also receive fresh tins to collect cigarette butts. The clinic staff will record information on hard copy case report forms during visits and will later be transcribed into an electronic system.

#### In-clinic evaluations

The first in-clinic evaluation for the smoking groups will be on days 12–15 (Figure 1, Table 4). Participants will check in on the evening of the first day and remain in the clinic until the evening of the final day. Participants will be instructed at check in on how to request cigarettes and return the butts within the clinic. During this and all other in-clinic evaluations, sufficient amounts of cigarettes for each smoker per day, transferred in participant-specific containers, will be made available by the site pharmacy and the clinic pharmacy staff and investigators will keep dispensing records. All cigarettes will be smoked only in a designated smoking area with appropriate ventilation.

**Table 4 T4:** Schedule for first in-clinic evaluation of smokers

**Day and suggested times**	**Sampling**	**Procedure**
**12**		
1700 h (check in)	Blood, urine	Measure BP, PR, RR and temperature; abbreviated physical examination and medical history; illicit drug, alcohol and cotinine testing; pregnancy testing; collection of diary and cigarette butts; dinner
1900 h	None	Start first 24 h urine collection, monitoring of cigarette consumption and collection of filters
2100 h	None	Snack
**13**		
0700 h	Blood	Measure BP, PR, RR and temperature; blood collection for creatinine in serum, biomarkers and gene expression
0800 h	None	Breakfast
To be scheduled	None	Assess smoking behaviour^a^
1000 h	None	Administer sensory, quality-of-life and diet and lifestyle questionnaires^b^
1200 h	None	Lunch
1500 h	None	Measure exhaled CO
1700 h	Saliva	Saliva cotinine testing; dinner
1900 h	None	End first and start second 24 h urine collection, monitoring of cigarette consumption and collection of filters
2100 h	None	Snack
**14**		
0700 h	Blood	Measure BP, PR, RR and temperature; blood collection for creatinine in serum, biomarkers and gene expression
0800 h	None	Breakfast
To be scheduled	None	Assess smoking behaviour^a^
1100 h	None	Pulmonary-function test
1200 h	None	Lunch
1500 h	None	Measure exhaled CO
1700 h	Saliva	Saliva cotinine testing; dinner
1900 h	None	End second 24 h urine collection, monitoring of cigarette consumption and collection of filters; switch to next assigned product
2100 h	None	Snack
**15**		
0700 h	None	Measure BP, PR, RR and temperature
0800 h	None	Breakfast
1000 h	None	Administer sensory questionnaire
1200 h	None	Lunch
1700 h	None	Dinner
1900 h	None	End filter collection; dispense interventional products and cigarette butt collection tins for use at home, remind participants of instructions for diet and completion of diaries

*BP,* blood pressure, *PR,* pulse rate, *RR,* respiratory rate *CO,* carbon monoxide, ^a^To be performed by sponsor. ^b^May be done on day 14.

On the evening of day 14, after completion of the 24 h urine collection, smokers will be switched to their next assigned product (control or RTP). Upon discharge on the morning of Day 15, participants will be given sufficient supplies of the new product and butt collection tins to last until the next visit. After switching, smokers will undergo four more in-clinic evaluations on days 45–46, 76–77, 108–109 and 181–183 (Tables 5 and 6).

**Table 5 T5:** Schedules for second, third and fourth in-clinic evaluations of smokers

**Days and suggested times**	**Sampling**	**Procedure**
**45, 76, 108**		
1700 h (check in)	Blood, urine	Measure BP, PR, RR and temperature; abbreviated physical examination and medical history; illicit drug, alcohol and cotinine testing; pregnancy testing; collection of diary and cigarette butts; clinical laboratory tests; electrocardiography; lung- function tests; dinner
1900 h	None	Start 24 h urine collection, monitoring of cigarette consumption and collection of filters
2100 h	None	Snack
**46, 77, 109**		
0700 h	Blood	Measure BP, PR, RR and temperature; measure creatinine in serum; biomarkers and gene expression
0800 h	None	Breakfast
1000 h	None	Administer sensory questionnaire; administer quality-of-life and diet and lifestyle questionnaires^a^
1200 h	None	Lunch
1500 h	None	Measure exhaled CO
1700 h	Saliva	Cotinine testing; dinner
1900 h	None	End 24 h urine collection, monitoring of cigarette consumption and collection of filters; dispense interventional products and cigarette butt collection tins for use at home, remind participants of instructions for diet and completion of diaries

*BP,* blood pressure, *PR,* pulse rate, *RR,* respiratory rate, *CO,* carbon monoxide, ^a^On day 108–109 visit only; may be conducted on either day.

**Table 6 T6:** Schedule for final in-clinic evaluation of smokers

**Day and suggested times**	**Sampling**	**Procedure**
***181***		
1700 h (check in)	Blood, urine	Measure BP, PR, RR and temperature; abbreviated physical examination and medical history; illicit drug, alcohol and cotinine testing; pregnancy testing; collection of diary and cigarette butts; dinner
1900 h	None	Start first 24 h urine collection, monitoring of cigarette consumption and collection of filters
2100 h	None	Snack
**182**		
0700 h	Blood	Measure BP, PR, RR and temperature; measure creatinine in serum; biomarkers and gene expression
0800 h	None	Breakfast
To be scheduled	None	Assess smoking behaviour^a^
1000 h	None	Administer sensory, quality-of-life and diet and lifestyle questionnaires†
1200 h	None	Lunch
1500 h	None	Measure exhaled CO
1700 h	Saliva	Cotinine testing; dinner
1900 h	None	End first and start second 24 h urine collection, monitoring of cigarette consumption and collection of filters
2100 h	None	Snack
**183**		
Anytime (check out)	None	Measure BP, PR, RR and temperature; physical examination; electrocardiography
0700 h	Blood	Measure creatinine in serum; biomarkers
0800 h	None	Breakfast
To be scheduled	None	Assess smoking behaviour^a^
1100 h	None	Pulmonary-function test
1200 h	None	Lunch
1500 h	None	Measure exhaled CO
1700 h	Saliva	Cotinine testing; dinner
1900 h	None	End second 24 h urine collection, monitoring of cigarette consumption and collection of filters; dispense adequate commercial products of normal ISO tar yield for 7 post-study days

*BP,* blood pressure, *PR,* pulse rate, *RR,* respiratory rate, *CO,* carbon monoxide, ^**a**^To be performed by sponsor. †May be done on day 183.

In previous smoking studies, most smokers (>90%) have increased the number of cigarettes they smoke on the last day of the study, typically by two to three cigarettes per day, which can adversely affect statistical outcomes. This increase is thought to be due to the impending end of the supply of free cigarettes. To mitigate this effect, at discharge from the last in-clinic evaluation, all smoking participants will be supplied with 7 days’ worth of their baseline product and asked to record daily consumption over the next 7 days. Participants will be contacted by telephone on the 7th day to obtain data on consumption.

In previous smoking studies based at the Hamburg clinic, it has been an absolute requirement of the ethics committee that smoking cessation counselling is provided to smoking subjects during the study. Therefore, several optional smoking-cessation workshops will be held during the study, for groups of 20–25 participants and led by a psychologist experienced in smoking cessation. The format will be a mix of lectures (including presentations, demonstrations and case studies), self-assessment (tests and questionnaires) and team and small-group work. The main aims of workshops will be to improve the knowledge of the participants about smoking cessation options, help participants to make realistic self-assessments regarding smoking cessation, increase participants’ motivation to quit or reduce smoking and develop individual plans for quitting or reducing smoking. Each workshop will take 60–90 min. Additionally, the Smoke-Free Programme of the Munich Institut für Gesundheitsförderung will be offered to all smoking subjects who wish to participate. The approach involves three meetings of 180 min and two telephone consultations. Following a preparatory phase, a day to quit smoking will be decided for all attendees. Strategies to handle irritation and critical situations and for behaviour control will be provided and alternative behaviours developed. In the final phase, the emphasis will be on prevention of relapse. Participants will be reminded of the dangers of smoking before enrolment, will be free to voluntarily quit smoking and withdraw from the study at any time and may still access the smoking-cessation workshops.

Ex-smokers and never smokers will be assessed in three in-clinic evaluations, on days 1–3, 78–80 and 162–164 (Figure 1, Table 7). As for the smoking groups, they will arrive in the evening of the first day and will remain in the clinic until the evening of final day of each visit.

**Table 7 T7:** Schedule for in-clinic evaluations of ex-smoker and never-smoker groups

**Day and suggested times**	**Sampling**	**Procedure**
**1, 78, 162**		
1700 h (check in)	Blood, urine	Measure BP, PR, RR and temperature; abbreviated physical examination and medical history; illicit drug, alcohol and cotinine testing; pregnancy testing; dinner
1900 h	None	Start first 24 h urine collection
2100 h	None	Snack
**2, 79, 163**		
0700 h	Blood	Measure BP, PR, RR and temperature; measure creatinine in serum; biomarkers and gene expression^a^
0800 h	None	Breakfast
1000 h	None	Administer quality of life and diet and lifestyle questionnaires^b^
1200 h	None	Lunch
1500 h	None	Measure exhaled CO
1700 h	Saliva	Cotinine testing; dinner
1900 h	None	End first and start second 24 h urine collection
2100 h	None	Snack
**3, 80, 164**		
0700 h	Blood	Measure creatinine in serum; biomarkers
0800 h	None	Breakfast
1000 h	None	Administer quality of life and
1100 h	None	Pulmonary-function test§
1200 h	None	Lunch
1500 h	None	Measure exhaled CO
1700 h	Saliva	Cotinine testing; dinner
1900 h	None	End second 24 h urine collection
**164 (check out)**		
Any time	Blood, urine	Measure BP, PR, RR and temperature; physical examination; electrocardiography; clinical laboratory tests

^a^Not on day 79. ^b^Not during visit on days 1–3; may be performed on day 79 or 80 and on day 163 or 164.

### Assessments

#### Cigarette consumption

Participants will be required to document cigarette consumption during ambulatory periods in diaries. In addition, on selected days, participants will be asked to collect the butts of smoked cigarettes in specially supplied tins and bring them to the next clinic visit. Butts will be counted to confirm the accuracy of diary entries on consumption. Participants will also be required to present any un-smoked cigarettes and the empty packets from smoked cigarettes. During in-clinic evaluations smokers’ cigarette consumption will be monitored by the clinic staff. Cigarettes will be issued to participants by staff one at a time, upon request, as they enter the designated smoking area and the butts of all smoked cigarettes will be collected by staff when smokers leave the smoking area.

#### Clinical and bioanalytical laboratory tests

The tests shown in Table 8 will be performed at screening for smokers and non-smokers. All tests, except for the HIV and hepatitis serology, will also be performed during the smokers’ in-clinic evaluation on days 108–109 and at the end of the study.

**Table 8 T8:** Clinical laboratory tests

**Haematology**	
●	Haemoglobin
●	Haematocrit
●	Total and differential leukocyte count (neutrophils, eosinophils, basophils, monocytes, lymphocytes)
●	Red-blood-cell count
●	Platelet count
●	Mean corpuscular volume
●	Mean corpuscular haemoglobin
●	Mean corpuscular haemoglobin concentration
**Clinical chemistry**	
●	Blood urea nitrogen
●	Creatinine^a^
●	Total bilirubin
●	Alkaline phosphatase
●	AST
●	ALT
●	Sodium
●	Potassium
●	Glucose (fasting)
●	Calcium
●	Chloride
●	Creatinine kinase
●	γ-glutamyl transpeptidase
●	Total protein
●	Uric acid
●	Urea
**Urinalysis (by sticks as part of clinical laboratory investigation)**	
●	pH
●	Specific gravity
●	Protein
●	Glucose
●	Ketones
●	Bilirubin
●	Blood
●	Nitrite
●	Urobilinogen
●	Leukocytes
●	**Additional tests**
●	Alcohol breath test^b^
●	Urine cotinine^b^
●	HIV
●	Hepatitis surface antigen
●	Hepatitis C virus
●	Urine drug screening^b^
	○ Amphetamines
	○ Barbiturates
	○ Benzodiazepines
	○ Cocaine
	○ MDMA
	○ Methamphetine
	○ Morphine
	○ Methadone
	○ Tricyclic antidepressants
	○ Tetrahydrocannabinol
●	Urine pregnancy test^b^

All tests, except the additional tests, will also be performed during the smokers’ day 108–109 in-clinic evaluations and at the end of the study.

^a^To be repeated in each 24 h in-clinic evaluation for all participants.

^b^To be repeated at all in-clinic evaluation visits for smokers and non-smokers.

##### Urine tests

Before the start of each 24 h urine collection period during in-clinic evaluations (Tables 5, 6, 7), each participant will be required to empty his or her bladder. Following this, each void will be collected in separate labelled brown plastic bottles and stored at 2-8°C. Collected urine will be pooled and stored at 2–8°C, labelled with the day on which collection ended. The total volume of urine collected over each 24 h period will be calculated from weight and specific gravity. After thorough mixing, samples will be transferred to labelled tubes and stored at −18 to −25°C. The details of biomarker assessments are shown in Table 9.

**Table 9 T9:** Urinary biomarkers

**Biomarker**	**Number and volume of aliquots**
4-Aminobiphenyl, 3-Aminobiphenyl,	2 aliquots of 12 mL each
o-Toluidine, 2-Aminonaphthalene	
OH-PAHs suite	2 aliquots of 12 mL each
Nicotine + 5	2 aliquots of 6 mL each
3-HPMA, HMPMA, CEMA	2 aliquots of 3 mL each
MHBMA	2 aliquots of 3 mL each
Total NNAL, NNN, NAB and NAT	2 aliquots of 10 mL each
F_2_-isoprostane (8-iso-PGF2 Type III)	2 aliquots of 6 mL each
F_2_-isoprostane (8-iso-PGF2 Type VI)	2 aliquots of 6 mL each
11-dehydrothromboxane B2	2 aliquots of 3 mL each
Urine mutagenicity	1 aliquots of 300 mL each
8-OHdG	2 aliquots of 1.5 mL each
Cis-thymidine glycol	2 aliquots of 1.5 mL each

*OH-PAH*, phenolic polycyclic aromatic hydrocarbons.*3-HPMA*, 3-Hydroxypropylmercapturic acid.

*HMPMA*, 3-hydroxy-1-methylpropylmercapturic acid. *CEMA*, 2-cyanoethylmercapturic acid.

*MHBMA*, monohydroxy-3-butenylmercapturic acid. *NNAL*, 4-(methylnitrosamino-1-(3-pyridyl)-1-butanol.

*NNN*, N-nitrosonornicotine. *NAB*, N-nitrosoanabasine. *NAT*, N-nitrosoanatabine.

*8-OhdG*, 8-Oxo-2′-deoxyguanosine.

Three haemoglobin adducts of identified smoke toxicants will be measured as BoED. Additionally, BoE that can yield information on short-term compliance, for example assessment of the ratio of a BoE for a smoke toxicant that does not change significantly between the products (such as nicotine) to a smoke toxicant that does significantly change (such as acrolein or NNK), will also be measured.

To ensure that every urine collection is complete for all participants, 24 h creatinine clearance will be calculated during the 24 h urine collection period. Creatinine clearance values will be verified by investigators, taking into account urine volumes and serum creatinine results. Values outside the normal clinical range (1.33–1.92 mL/s/m^2^) may be classified as acceptable, since values have been reported to vary greatly between individuals and a substantial proportion are likely not to fall within this range.

Samples available for long-term storage after the study will be kept at the sponsor’s biological sample archive.

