### Previous clinical study assessments

The tools to assess exposure to smoke toxicants were examined in two previous clinical studies conducted in Germany and Canada using conventional cigarettes. These studies aimed to assess whether the available techniques could adequately assess human smoke exposure by filter analysis and measurement of biomarkers of exposure (BoE) [9-11]. These enable the exposure tobacco smoke toxicants or their metabolites to be measured in urine, or other biologic matrices. Both studies showed a good correlation between exposure estimates from the two methods, and, in the case of the German study, the methods were senstive enough to detect changes in smoke exposure following a switch to a cigarette with a lower International Organization for Standardization (ISO) tar yield [10].

Technologies used in the RTPs have previously been shown to significantly reduce yields of a range of tobacco smoke toxicants by 10% to 95% compared with typical commercial products with equivalent ISO tar yields [12]. A clinical study of these RTPs, using a short-term (6-week) switching design, determined smoke toxicant exposure by measurement of various BoE in current smokers after they switched from conventional cigarettes to an RTP (ISRCTN 72157335) [13]. This study showed that toxicant exposure was reduced after switching to the RTP, although the prototypes required further development to optimise the reductions and improve acceptability to smokers.

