### Study participants

#### Identification of study participants

Participants will be recruited into the study through advertisements on the clinic’s own website and local advertising that will not refer to the characteristics of the study products. All study participants (smokers and non-smokers) will be sourced from the Hamburg area from the same communities. Adult, healthy participants of either sex and of any ethnic origin will be enrolled. The planned ratio of male to female participants within each subgroup of the smoking groups is between 3:2 and 2:3, that is, an attempt will be made to enrol approximately equivalent numbers of male and female subjects into each subgroup, within these tolerances.

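### The creatinine-clearance range for checking 24 h urine completeness is very probably mis-scaled by 1.73, and with its waiver the check has little power to detect incomplete collections

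*Protocol article*

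**What the plan says.** The Urine tests section of the protocol article gives the purpose of the check: "To ensure that every urine collection is complete for all participants, 24 h creatinine clearance will be calculated during the 24 h urine collection period". The decision is left to judgement: "Creatinine clearance values will be verified by investigators, taking into account urine volumes and serum creatinine results". The only reference figure is then stated and waived in one sentence: "Values outside the normal clinical range (1.33–1.92 mL/s/m^2^) may be classified as acceptable". The reason given is that "values have been reported to vary greatly between individuals and a substantial proportion are likely not to fall within this range".

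A footnote to Table 8 on creatinine says "To be repeated in each 24 h in-clinic evaluation for all participants", so the data for a clearance value exist at every in-clinic evaluation. The population is described under Identification of study participants: "Adult, healthy participants of either sex and of any ethnic origin will be enrolled".

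Two other places bear on the point. Investigational products says that pharmacy staff and investigators can tell the cigarettes apart by codes printed on packs and cigarettes. Table 1 shows that every primary biomarker of exposure except salivary cotinine and exhaled CO is measured in urine, as is F2-isoprostane among the primary biomarkers of biological effect.

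**The concern.** A range described as normal should contain most complete collections from healthy adults. The printed one would do so only if their clearances were unusually high, which suggests that a body-surface factor was dropped. If most complete collections fall below the lower limit, a low reading no longer points to lost urine.

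The waiver then removes what force remains. An in-range value has no stated consequence, and an out-of-range value may be accepted case by case.

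The stake is the set of primary urinary biomarkers. If they are analysed as 24 h amounts, lost urine lowers the result in proportion, which is the direction of the study hypothesis. The article calculates total 24 h volume, which suggests amounts, but its Statistical analysis section speaks of concentrations and levels, so this is an assumption. Because acceptance rests on people who can identify the product, acceptance that differs between groups is possible.

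**Working it through.** **Inputs.** From Urine tests: limits of 1.33 and 1.92 mL/s/m². The article gives no source for the range, no body surface area and no other clearance figure, so its derivation cannot be reproduced from the document. Two inputs are therefore assumptions: a source range of 80–115 mL/min per 1.73 m², and true clearances of 80–140 mL/min per 1.73 m² in healthy adults.

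**Step 1: where the digits may come from.** 80/60 = 1.333 and 115/60 = 1.917. Both printed limits follow from 80–115 mL/min by converting minutes to seconds, with no division by 1.73.

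**Step 2: what the range means as printed.**
- 1.33 × 60 × 1.73 = 138.1 mL/min per 1.73 m²
- 1.92 × 60 × 1.73 = 199.3 mL/min per 1.73 m²

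Read per 1.73 m² instead, the limits are 1.33 × 60 = 79.8 and 1.92 × 60 = 115.2 mL/min. The two readings differ by exactly 1.73.

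**Step 3: what collections would read in the printed unit.** A complete collection reads C/60/1.73, where C is true clearance in mL/min per 1.73 m². Clearance is urinary creatinine amount divided by serum concentration and time, so losing a fraction f of the urine multiplies the reading by (1 − f). The last column uses f = 0.25 for illustration.

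| Assumed C | Complete, mL/s/m² | 25% lost, mL/s/m² |
|---|---|---|
| 80 | 0.77 | 0.58 |
| 100 | 0.96 | 0.72 |
| 115 | 1.11 | 0.83 |
| 130 | 1.25 | 0.94 |
| 140 | 1.35 | 1.01 |

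A complete collection reaches 1.33 only when C is at least about 138. From 80 to 130, both columns lie wholly below the printed lower limit. A reading of 0.90, for example, fits a complete collection at C = 0.90 × 60 × 1.73 = 93, or a loss of 1 − 0.90/1.25 = 28% at C = 130.

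**Step 4: what remains if the unit is corrected.** The largest loss that stays in range, for a participant whose complete collection would read x in the unit of the limits, is 1 − 1.33/x.
- Lower limit, x = 1.33: 0%
- Mid-range, x = (1.33 + 1.92)/2 = 1.625: 1 − 1.33/1.625 = 18%
- Upper limit, x = 1.92: 1 − 1.33/1.92 = 31%

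These fractions do not depend on the unit, because 1.73 cancels.

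**Step 5: the limits rescaled.** 1.33/1.73 = 0.77 and 1.92/1.73 = 1.11 mL/s/m².

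**Step 6: data for a within-participant check.** Tables 4 to 6 give smokers 2 + 1 + 1 + 1 + 2 = 7 collections. Table 7 gives non-smokers 3 × 2 = 6.

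**The case against.** The strongest reply is that nothing in the article contradicts the printed unit. It holds one clearance range only, and calling that range wrong relies on an outside notion of normal clearance; a factor of 1.73 may also have been lost when the full protocol was condensed. This stands, and it is why the unit is put as very probable and as a query to the sponsor. The inference does survive a wide assumption, since every true clearance below about 138 mL/min per 1.73 m² gives the same result.

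Second, the range is not a pass/fail gate. Investigators also weigh urine volume and serum creatinine, so no collection is accepted or rejected on 1.33 alone. This stands too, and correcting the unit alone would change no stated decision. But it leaves the check without any operative criterion in the article. A fixed rule may sit in the full protocol, which is not shown; the point here is that the article prints a criterion and then sets it aside.

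Third, there are safeguards. Collections are residential, start from an emptied bladder, and each void is bottled separately. The planned ratios of one biomarker of exposure to another would cancel lost urine. There is a concurrent non-switching group, and loss that is similar in both groups creates no difference between them. All of this stands and limits the likely harm. The article gives no evidence that large losses occur or that they differ between groups.

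Fourth, the article attributes its tolerance to variation between individuals. A reader might infer that the mis-scaled range is what prompted the waiver; the text does not show that.

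**Conclusion.** The point holds in limited form, with medium confidence. The printed range is very probably too high by a factor of 1.73. On assumed true clearances of 80–130 mL/min per 1.73 m², complete collections read 0.77–1.25 mL/s/m² against a printed lower limit of 1.33. Together with the waiver and unblinded judgement, this leaves the stated check with little power to separate complete from incomplete collections.

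Three stronger readings are tempting and are not supported:
- **That the check passes collections missing 31% of the urine.** That figure applies only to a participant whose true clearance sits at the upper limit; it is 18% at mid-range and 0% at the lower limit. Being in range is also not the same as being passed.
- **That the primary endpoints are left unprotected.** The residential procedures, the control group and the non-urinary primary endpoints count against this, and differential loss is not shown.
- **That the possible loss should be set against the smoke-yield reductions in Previous clinical study assessments, "by 10% to 95% compared with typical commercial products".** Those are product-level yields from earlier work across many toxicants. A loss in one participant's collection is a different quantity.

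**What to change.** 1. Confirm the unit against the laboratory source. If it is a slip, state the range per 1.73 m², or as 0.77–1.11 mL/s/m².
2. Add a within-participant check. Compare each collection's total 24 h urinary creatinine with the median of that participant's other collections, and flag it below a pre-set fraction. A fraction of 75% is only an example: it tolerates up to 25% loss, so the choice should be justified. The check cannot detect under-collection that is constant across visits.
3. Have the flag set by someone who does not know the product.
4. Run one sensitivity analysis of the primary urinary biomarkers, either excluding flagged collections or expressing results per gram of creatinine.

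The cost is a corrected unit, one rule and a small extra analysis. Urine volume and creatinine are already measured for the planned clearance calculation, so no new samples are needed.
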